##### Process evaluation

**Participant, educator, and performance site coordinator-level process evaluation.** A process evaluation will assess intervention dose delivered, dose received, and fidelity [97]. “Dose delivered” will be determined based on CSA share pick-up and lesson attendance. Participating farms will provide data on CSA share pick-up. Participants will complete an identifiable, paper-based questionnaire after each of the nine lessons to report their utilization of CSA share contents and their perceived utility of lesson components (“dose received”). Utilization also will be determined through a question on the fall online questionnaire which asks the portion of the share usually eaten. For households that report that they did not usually eat all of their share, follow-up questions related to preservation, spoilage, and food sharing will be asked. “Fidelity” will be assessed via post-lesson educator questionnaires and site coordinator quality assurance (QA) visits. Educators will report their fidelity to the written curriculum and their perceptions of the lesson’s acceptability, feasibility, and adaptability. Performance center coordinators will conduct two QA visits to each community during Years 2 and 3 and will audit that week’s CSA share pick-up and lesson facilitation. Audits will be used to collect information on the functionality of pick-up sites and CSA share contents. Class observations will be used to supplement educator’s reporting of lesson fidelity and to assess educators’ exhibition and use of qualities and techniques deemed important for adult education: preparedness, adaptability, knowledge, facilitation of group cohesion, respect, and promotion of a safe environment, immediacy of content and engagement. Following the CSA season, participant focus group discussions and educator interviews will be conducted to explore and elaborate upon findings from the above-described questionnaires.

**Program cost assessment.** F3HK program administration costs will be assessed via an 8-question questionnaire completed by performance center coordinators and relevant study personnel at the end of each CSA season. The questionnaire will assess the following cost categories: salaries, wages, and benefits; facilities and utilities; equipment, supplies, and travel; and staff training. These data will be used with the “costs associated with CO-CSA participation” data to determine the total value of resources used during administration of and participation in the F3HK program.

**Non-participation assessment.** Brief phone interviews including quantitative and qualitative questions will be used to understand the reasons eligible families choose not to participate in F3HK and the reasons why enrolled families cease participation (defined as missing four or more share pick-ups).

#### Unexpected events reporting procedure

Our unexpected events reporting procedure will require that the coordinating center be contacted any time a research staff member, nutrition educator, farmer, or research participant reports or observes a research participant or child experience an injury (e.g. a cut or fall) during the CO-CSA pick-up or education curriculum delivery, or that something occurs that could compromise participant privacy. The Principal Investigator ([name]) determines whether this event was a serious adverse event and, if so, the Cornell IRB will be notified within five business days or, if not, the event will be included on the normal reporting schedule.

#### Protocol amendments

The study protocol is consistent with the SPIRIT guidelines for clinical trials [98] (Additional file 2). Any protocol amendments will be developed with input from all co-investigators, and will be reviewed and approved by the University of Vermont and Cornell University IRBs prior to implementation. A written protocol document will be updated as needed and stored on a secure drive to which only members of the research team will have access.

#### Data management and analytic plan

##### Data management

Most data will be entered online directly by participants. All information collected will be kept private and confidential, and stored on a secure computer to which only members of the research team will have access. Participant’s names and all personal identifiers will be removed from data before analysis. All personal identifiers will be encrypted and password protected.

##### Analysis of primary and secondary intervention outcomes

Intent-to-treat analyses will allocate all participants to initial random assignment group for measurement at Year 2 baseline, Year 2 fall assessment, and Year 3 spring assessment. Subsequently, Group 2 will be considered to have received the intervention for measurement at Year 3 fall assessment, Year 4 spring assessment, and Year 4 fall assessment. Likewise, Groups 3 and 4 will maintain initial random assignment for measurement at Year 3 spring assessment, Year 3 fall assessment, and Year 4 spring assessment, but then Group 4 will be considered to have received the intervention for Year 4 fall assessment.

Change variables for linear outcomes (Table 4) will be created by subtracting the baseline from the measurement at the end of the CSA season, as well as during subsequent measurement points. Multilevel linear models with fixed and random effects will be used because observations are repeated measures for participants nested within farm communities. Models also will include intervention group status, baseline measures of outcome variables, and relevant covariates. Additional models will control for CO-CSA and education dose received. Multiple imputation will be used to estimate partial missing data.

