Each state will recruit 60 participants within at least two CSA programs. Participants will enroll in the CO-CSA for two seasons and participate in the CSA-tailored education during the first season. We will randomize families into either the intervention or control (delayed intervention) group. Group 1 (intervention) families will participate in the CO-CSA plus tailored education in Year 2 and Year 3; Group 2 (control) families will receive the same CO-CSA plus tailored education in Year 3 and Year 4 (Table 3). A delayed parallel design was selected in order to keep the benefits of participation, and therefore the motivation to keep participating, equivalent for parallel groups. We will work with participating farmers to support the transition to alternative funding for the cost-offset following completion of the intervention. Participants will be asked not to enroll in a CSA outside of the study. Participants may enroll in other nutrition education at any time during the trial. Data will be collected at identical time points for all participants. Bi-annual engagement postcards or letters will be mailed to all participants with the aim of increasing retention.

**Table 3 Tab3:** Delayed intervention design for component 4 (randomized trial)

	Year 2	Year 3	Year 4
Group 1 – intervention	CO-CSA + Education	CO-CSA	Sustainability
Group 2 – control	Data collection only	CO-CSA + Education	CO-CSA
Group 3 – intervention		CO-CSA + Education	Sustainability
Group 4 – control		Data collection only	CO-CSA + Education

In Year 3, to compensate for study attrition, we will recruit additional participants and randomly assign into an identical intervention of shorter duration or control (delayed intervention). Group 3 (intervention) families will participate in the CO-CSA plus tailored education in Year 3 only; while Group 4 families will receive the same CO-CSA plus tailored education in Year 4 only. The study timeline is presented in Fig. 1.

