##### Physical measures

Anthropometric and dermal measures will be collected at baseline and in the fall of Years 2–4.

**Anthropometric measures.** Anthropometric measures will be taken without shoes and in light clothing according to standard procedures [81]. Weight will be measured to the nearest 0.2 lbs. using the Seca Clara 803 scale. Height will be measured to the nearest 0.125 in. with the Seca 213 portable stadiometer. Weight and height measurements will be collected in duplicate unless the two measurements are more than 0.4 lbs. or 0.125 in. apart. In that case, a third measurement will be taken.

**Dermal carotenoid measures.** Dermal carotenoid levels will be assessed as an objective measure of fruit and vegetable intake. Study staff will use the Pharmanex Biophotonic Scanner S3 (NuSkin, Provo, UT), which non-invasively measures the concentration of carotenoids in skin tissues using resonance Raman spectroscopy, to scan a specific point of the palm of one hand. Dermal carotenoids will be measured in duplicate, unless the two measurements are greater than 2000 units apart. In that case, a third measurement will be taken. The same hand will be used at each assessment.

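### Control families are recoded as intervention after crossover under an intent-to-treat label, so the primary contrast is not confined to the randomised comparison

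*Protocol article*

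**What the plan says.** The section on analysis of primary and secondary intervention outcomes opens with intent-to-treat analyses that "allocate all participants to initial random assignment group for measurement at Year 2 baseline, Year 2 fall assessment, and Year 3 spring assessment". It then changes the rule for the first cohort: "Group 2 will be considered to have received the intervention for measurement at Year 3 fall assessment, Year 4 spring assessment", and likewise at Year 4 fall. For the Year 3 top-up cohort, "Groups 3 and 4 will maintain initial random assignment for measurement at Year 3 spring assessment, Year 3 fall assessment, and Year 4 spring assessment", and Group 4 is coded as intervention at Year 4 fall.

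The outcomes are changes from baseline at the end of the season and at later points. On the model it says "Multilevel linear models with fixed and random effects will be used because observations are repeated measures for participants nested within farm communities" and "Models also will include intervention group status, baseline measures of outcome variables, and relevant covariates". No visit, season, calendar-year or age term is named.

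Table 3 gives Group 1 a share with classes in Year 2, a share without classes in Year 3 and a sustainability year in Year 4. For the top-up cohort, "Group 3 (intervention) families will participate in the CO-CSA plus tailored education in Year 3 only", so its Year 4 is also a sustainability year.

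Some primary outcomes have no spring value: "Anthropometric and dermal measures will be collected at baseline and in the fall of Years 2–4", and Table 5 places the dietary recalls at baseline and fall only.

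**The concern.** Intent-to-treat normally means that records stay with the randomised arm. Here that holds only until the control arm starts the programme. Afterwards Groups 1 and 2 carry the same code, and any information about the intervention from their records is before-after or cross-cohort.

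Two things follow if those records feed the headline estimate.

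- **Drift.** Control-coded records sit early in follow-up and intervention-coded records sit late. Without time terms, any change with age or calendar time moves the status coefficient. Group 2's change at Year 3 fall also runs from a baseline that precedes a whole untreated year, and fall-only outcomes have no spring value to serve as a fresh baseline.
- **Mixed exposure.** One intervention code covers the first season with classes, the second season without them, the sustainability year and off-season spring visits. Its coefficient is a weighted mixture with no clear meaning unless the effect is the same in all of them.

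**Working it through.** **1. Status coding implied by the analysis section and Table 3** (I = coded intervention, C = coded control)

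| Assessment | Group 1 | Group 2 | Group 3 | Group 4 |
|---|---|---|---|---|
| Year 2 fall | I, season 1 | C | – | – |
| Year 3 spring | I, off-season | C | entry | entry |
| Year 3 fall | I, season 2 | I, season 1 | I, season 1 | C |
| Year 4 spring | I, off-season | I, off-season | I, off-season | C |
| Year 4 fall | I, sustainability | I, season 2 | I, sustainability | I, season 1 |

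At Year 3 fall and Year 4 spring the only controls are Group 4, who were randomised against Group 3 alone. At Year 4 fall nobody is coded control.

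**2. Share of post-baseline records with no randomised control in their own cohort**

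Groups 1/2: 3 of 5 visits (60%), or 2 of 3 (67%) for fall-only outcomes. Groups 3/4: 1 of 3, or 1 of 2 for fall-only outcomes. The size of Groups 3/4 and attrition after the first season are not given, so I varied both.

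- No loss, 60 households added: (240 × 3 + 60 × 1) / (240 × 5 + 60 × 3) = 780 / 1380 = 56.5%. With 120 added: 840 / 1560 = 53.8%.
- 25% lost every season, none added: Groups 1/2 supply 180, 180, 135, 135 and 101.25 records, so (135 + 135 + 101.25) / 731.25 = 50.8%. With 60 and 120 added: 47.4% and 44.8%.
- Fall-only outcomes run from 52.9% (25% loss per season, 120 added) to 67% (no loss, none added).

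The range is therefore about 45–60% for all-visit outcomes and 53–67% for fall-only outcomes.

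**3. Drift, if one status coefficient is fitted without time terms**

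Assumptions, none of them in the article: no true effect; linear drift of D SD per year; visits at 0.4, 1.0, 1.4, 2.0 and 2.4 years, with Groups 3/4 entering at 1.0; 90 per arm in Groups 1/2 at every visit (120 less the stated 25%); 30 per arm in Groups 3/4; unit variance; within-person correlation 0.5. The expected coefficient is the status element of (ΣX′V⁻¹X)⁻¹ΣX′V⁻¹μ, where μ is D times the time since the family's own baseline and V is compound-symmetric.

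The result is 1.07 × D with SE 0.060. The rejection probability is Φ(δ − 1.96) + Φ(−δ − 1.96) with δ = 1.07D / 0.060.

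| D (SD/year) | Spurious effect (SD) | δ | False-positive rate |
|---|---|---|---|
| 0.05 | 0.05 | 0.89 | 15% |
| 0.10 | 0.11 | 1.78 | 43% |
| 0.20 | 0.21 | 3.57 | 95% |

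At D = 0.1, a top-up of 0–60 per arm and correlations of 0.3–0.7 give 31–66%. A wider set (no loss or 25% per season; 0, 60 or 120 households added; all-visit or fall-only outcomes) gives a bias of 0.85–1.45 × D, that is 0.09–0.15 SD, and 18–80%.

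**4. With visit and cohort terms added**

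Drift bias becomes 0.00 and the false-positive rate 5%. Exposure mixing remains. Assume a true 0.5 SD effect in active share seasons and none in spring or the sustainability year. The coefficient is then 0.39 SD over all visits (0.33 without the time terms) but 0.66 SD for fall-only outcomes. It overshoots in the second case because Groups 1 and 3 decline while still coded treated. The Year 4 fall effect absorbs that decline, which makes the newly treated families look better.

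**5. What the randomised contrast can carry**

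First, the article's sample size: 63 per arm for 0.5 SD at 80% power; design effect 1 + 9 × 0.05 = 1.45 with 10 households per arm per community; 63 × 1.45 / 0.75 = 122 per arm, 244 in total against the stated 240. Other readings of the design effect are possible. On this one, Year 2 fall alone keeps 120 × 0.75 = 90 per arm, or 90 / 1.45 = 62 effective. Then 0.5 × √(62/2) = 2.78 and Φ(2.78 − 1.96) ≈ 0.80.

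**The case against.** A reader might infer that the article commits to a single pooled status coefficient with no time terms. It does not. It speaks of models in the plural, with fixed and random effects and relevant covariates. Visit effects, visit-specific contrasts or age at assessment would all fit that wording, and a condensed article may leave them to an analysis plan that is not shown. The false-positive rates are therefore conditional on a model that the text allows but does not state. They also depend on a drift rate, a correlation and a top-up size that I assumed. Child BMI percentile and energy intake as a percentage of requirement are already referenced to age.

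A reader might also infer that most records, or all later visits, lack a concurrent randomised control. That holds for the planned schedule in Groups 1/2 and for fall-only outcomes. Overall the share can fall below half, and Group 4 is a genuine control at Year 3 fall and Year 4 spring.

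Nor can one infer that the effect is known to be diluted. Farms must agree to a plan for continuing the reduced-price shares, the study supports the move to other funding, and skills and kitchen tools may last. No effect outside active seasons is an assumption.

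Finally, the randomised comparison is visible in the text: the pre-crossover visits keep initial assignment, and the cost-effectiveness section contrasts baseline-to-late-season change between the arms. The article calls the trial exploratory, and using post-crossover data is legitimate in a delayed-intervention design.

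All of this limits the severity. It does not remove the point, because the recoding rule and its label are stated outright, and time terms alone do not separate the programme phases.

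**Conclusion.** The concern holds in a limited form. The article fixes a coding that leaves the randomised contrast after crossover, calls it intent-to-treat, and does not say that the primary result comes from the pre-crossover visits. About 45–60% of post-baseline records (53–67% for fall-only outcomes) have no randomised control in their own cohort, and Year 4 fall has no control-coded family.

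The harm depends on the model eventually fitted. Without time terms, an assumed drift of 0.1 SD per year gives a bias of about 0.1 SD, roughly a fifth of the 0.5 SD target. With visit and cohort terms that bias disappears, but the estimate can still be too low or too high if effects do not fully persist. The pre-crossover contrasts are unaffected, and so is the sample size. Should-fix, with moderate confidence.

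**What to change.** State that the primary contrast is the randomised first-season comparison: Group 1 v Group 2 at Year 2 fall and Group 3 v Group 4 at Year 3 fall, in one baseline-adjusted multilevel model with arm, community and cohort terms. Treat the pre-crossover spring visits (Year 3 spring for Groups 1/2, Year 4 spring for Groups 3/4) as secondary.

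Analyse post-crossover records separately, with visit and cohort effects and with exposure terms that distinguish first season, second season, sustainability year and off-season spring. Label these analyses non-randomised and reserve intent-to-treat for the pre-crossover contrasts.

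This needs wording only and no new data. The cost is fewer records in the headline estimate. With 25% lost per season, 60 households added and a within-person correlation of 0.5, the standard error for a fall-only outcome is 0.133 SD, against 0.111 SD for the pooled model with visit and cohort terms (unit variance, before baseline adjustment or any design effect). The 0.5 SD target is still 0.5 / 0.133 = 3.8 standard errors.

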##### Process evaluation

Logistic regression models will be used to assess whether differences in intervention implementation across sites (via “fidelity” measures) and differences in experiences between participants (via “dose delivered” and “dose received” measures) influence participants’ outcomes. Qualitative assessments of participants’ and educators’ experiences will be used to understand factors associated with dose and fidelity at each site. Data on non-participation will be analyzed using the Five Dimensions of Access framework [99]. Results will inform the use and refinement of the curriculum and CO-CSA model for future community-based nutrition interventions and will be helpful for CSA farmers interested in incorporating the CO-CSA model into their business operations.

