**Fruit and vegetable availability and accessibility within the home.** Home fruit and vegetable availability will be assessed using questions from a 3-item scale, which asks caregivers “How often are the following true? 1) We have fruits and vegetables in my home, 2) In my home, vegetables are served at meals, 3) In my home, fruit is served for dessert” [88]. Home fruit and vegetable accessibility will be assessed using questions from a 4-item scale, which asks caregivers, “How often are the following true? 1) In my home, there is fruit available to have as a snack, 2) In my home, there is vegetable available to have as a snack, 3) In my home, there are cut-up vegetables in the fridge for my child to eat, and 4) In my home, there is fresh fruit on the counter, table, or somewhere else where my child can easily get to it” [88]. For both scales, four ordinal response options will be offered (hardly ever, rarely, sometimes, often). Caregivers also will be asked to report how easy or difficult it is to financially afford and physically access acceptable quality fruits and vegetables from five ordinal response options.

**Household food security.** Household food security will be classified by the 6-item short form of the USDA Food Security Survey Module (FSSM), with a 30-day reference period [89]. Items ask respondents about the conditions and experiences of food insufficiency due to resource limitations, and the behavioral responses of household members to these conditions. The form will be converted to an online format, but questions and response options will not be modified. Participants that affirm two or more items are considered to live in a food insecure household.

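### Logistic regression is prescribed for relating fidelity and dose to participants' outcomes, although most of those outcomes are continuous and have no binary version defined

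*Protocol article*

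**What the plan says.** Two neighbouring sections of the protocol article's analytic plan for Component 4 bear on this.

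- **Analysis of primary and secondary intervention outcomes.** "Change variables for linear outcomes (Table 4) will be created by subtracting the baseline from the measurement at the end of the CSA season". The model is then chosen with its reason: "Multilevel linear models with fixed and random effects will be used because observations are repeated measures for participants nested within farm communities". The section adds: "Additional models will control for CO-CSA and education dose received".
- **Process evaluation (analysis).** "Logistic regression models will be used to assess whether differences in intervention implementation across sites" (the fidelity measures) and differences between participants (the two dose "measures) influence participants’ outcomes". No outcome is named, no cut-point is given, and clustering is not mentioned.

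The measurement level comes from the Process evaluation text under data collection. Fidelity "will be assessed via post-lesson educator questionnaires and site coordinator quality assurance (QA) visits", so it belongs to the educator or site. Dose delivered is share pick-up and lesson attendance. For dose received, "Participants will complete an identifiable, paper-based questionnaire after each of the nine lessons to report their utilization of CSA share contents". Both dose measures belong to the family.

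Table 4 lists as primary outcomes the child's fruit and vegetable intake, beverage and snack intake, energy intake as a percentage of requirement, dermal carotenoids and diet quality. One secondary outcome is given an explicit two-way classification, household food security: "Participants that affirm two or more items are considered to live in a food insecure household".

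**The concern.** A logistic model needs a binary (or ordered) response. The outcomes of main interest are quantities, and the preceding section treats them as such. To follow the Process evaluation text for these outcomes, the analyst must cut each change score at a point that the article does not define. This has two consequences. Information is discarded, so a real relation between dose or fidelity and diet is easier to miss. The threshold could also be chosen after the data are seen.

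What is at stake is limited but practical. The article says that these results will guide refinement of the curriculum and of the cost-offset model, and this is the only place where it names a quantitative analysis of implementation differences between sites.

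**Working it through.** **Inputs.** From Sample size calculations: 240 households (120 + 120), 12 communities of 20, ICC 0.05, 25% attrition, effect 0.5 SD, power 0.8, 95% confidence. From Randomization: 1:1 allocation within communities, hence 10 families per arm per community. Assumptions made here: a normally distributed outcome, equal site sizes and one fidelity score per site.

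**1. The plan's own figure.** The process analysis has no sample size of its own, so the trial's figure is checked. Two means differing by 0.5 SD, two-sided 5%, 80% power: 63 per arm. Design effect with 10 per arm per community: 1 + (10 − 1) × 0.05 = 1.45. Then 63 × 1.45 / 0.75 = 121.8, or 122 per arm and 244 in total. The stated 240 is reproduced to within 2%, so the inputs can be used as they stand.

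**2. Families available.** Intervention arm after attrition: 120 × 0.75 = 90, or 7.5 per community. Both arms: 180, or 15 per community.

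**3. Information lost by splitting.** When a normal outcome is cut so that a proportion p lies below the cut, the share of information kept is φ(q)² / [p(1 − p)], where q is the p-quantile.

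| Split | Information kept | Sample needed to compensate |
|---|---|---|
| 50/50 | 2/π = 0.637 | × 1.57 |
| 75/25 | 0.539 | × 1.86 |
| 90/10 | 0.342 | × 2.92 |

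The median split is the best case: 90 × 0.637 = 57 families in effect.

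**4. Power for a family-level dose association.** Simulation, 3,000 runs per case, families independent:

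| Families | Correlation | Linear | Logistic, 50/50 | Logistic, 75/25 |
|---|---|---|---|---|
| 90 | 0.29 | 79-80% | 60% | 50% |
| 180 | 0.207 | 80% | 60% | 53% |

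**5. Conditional check on clustering (site-level fidelity, 12 communities).** This applies only if the logistic model has no community term. The ICC of 0.05 refers to the continuous scale. After a median split of a normal outcome it becomes (2/π) × arcsin(0.05) = 0.032.

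- 7.5 per site: design effect 1 + 6.5 × 0.032 = 1.21; false-positive rate 2 × [1 − Φ(1.96/√1.21)] ≈ 7%.
- 15 per site: design effect 1 + 14 × 0.032 = 1.45; false-positive rate ≈ 10%.

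Simulation of a single-level logistic model (4,000 runs each) gives 7.3% at 8 per site, 8.3% at 10 and 9.4% at 15. Regression on the 12 site means stays at 4.8-5.2% for the same site sizes.

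**The case against.** The strongest reply is that the Process evaluation text speaks only of participants' outcomes and does not cite Table 4. The preceding section confines its change scores to linear outcomes, which implies that some outcomes are not linear. Household food security is binary and caregiver knowledge is recorded as ordinal items, and logistic models suit these. On that reading the article merely fails to say which outcomes are modelled logistically. Part of this stands: not every outcome is continuous, and logistic models should be kept where they fit. It does not remove the point, because logistic regression is the only quantitative method named for this question and nothing restricts it to binary outcomes.

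Dose received also enters the additional multilevel linear models, so continuous information on dose is not wholly lost. That is correct and lessens the harm for dose. The article says nothing similar for fidelity.

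A reader might also infer two stronger things that the documents do not support:

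- **That clustering is ignored and standard errors are therefore too small.** The article is silent on this. A logistic model can carry a community random effect, the nesting is acknowledged in the section just before, and a condensed article may leave such detail to the analysis plan. The inflation in step 5 is therefore conditional. It concerns fidelity and much less family-level dose.
- **That this is the only quantitative route to Objective 3.** Objective 3 contrasts operational characteristics of CSA models, whereas fidelity here is mainly adherence to the lessons. The article never ties this analysis to that objective.

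**Conclusion.** The concern holds in a limited form. The article positively prescribes a model type that does not fit the primary and most secondary outcomes, and this differs without explanation from the model it gives those outcomes one section earlier. Under normality the cost is at least 36% of the information, and a fall in power from about 80% to about 60% at the most favourable cut. That cost arises with any logistic model of a split outcome, with or without a community effect.

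The false-positive rate of roughly 7-10% for fidelity depends on three things: a single-level model, ICC 0.05, and about 8 to 15 families at each of 12 sites. Using the unsplit ICC for a split outcome would give 9-13% for 7.5 to 15 families per site, which is too high. The point is minor: it touches a secondary process analysis and leaves the randomised comparison as it is.

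**What to change.** In the Process evaluation paragraph of the analytic plan, replace the general reference to logistic regression. For continuous outcomes, use the baseline-adjusted multilevel linear model of the preceding section, with fidelity as a community-level covariate, dose as a family-level covariate and a random intercept for community. Keep (mixed) logistic or ordinal models for outcomes that are binary or ordinal, such as household food insecurity, and name those outcomes.

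The cost is a sentence or two of wording and no new data. Intervals for site-level fidelity may be wider, because they will reflect about 12 communities rather than the number of families.
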